### Ethics approval and dissemination of results

The study adheres to Good Clinical Practice guidelines. The protocol has been approved by the Committee on Health Research Ethics of the Capital Region of Denmark (approval date: 21.07.2020, identifier: H-20011650) and by the Danish Data Protection Agency (approval date: 18.05.2020, identifier: P-2020-566). The study is registered on clinicaltrials.gov (identifier: NCT04410315). Amendments to the protocol will be communicated to the relevant authorities.

The results of the study (positive, negative, or inconclusive) will be published in a peer reviewed journal. The results will also be presented in relevant conferences. Reporting will be guided by “Strengthening the Reporting of Observational Studies in Epidemiology Statement”.

## Trial status

The study has been recruiting patients since the 1^st^ of August 2020. We estimate a trial recruitment period of 18–20 months.

## Bias and confounders

Selection bias is almost always present in studies with voluntary participation. Factors such as socioeconomic status, psychological resilience, severity of illness and number of comorbidities may influence the patient’s readiness to participate. The published data will therefore include the number of non-participants.

Furthermore, patients are included consecutively, in the order in which the studies are mentioned.

Since investigators are susceptible to observational bias, a flowchart and standardized questioning will be used for mRS assessment.

We expect minimal loss to follow-up regarding mortality, as this information will be accessed through the Danish Cause of Death Register. Because many patients may die during the follow-up, survivorship bias is an important type of bias and will be corrected for as appropriate.

The measurement error of S-lactate is expected to be minimal, since all blood samples are analyzed with the same type of equipment.

Major factors influencing lactate production and metabolism are investigated in the study as exploratory endpoints. Continuous variables, such as vital data, are measured on the same type of monitor for all patients. To avoid misclassification, tumors will be classified using the 10^th^ version of International Classification of Disease and the World Health Organization’s classification of tumors, based on the histopathological conclusion from the intraoperative biopsy. The standardized case report form will be publicized as a supplement to study results. Missing data and number of patients lost to follow-up will be reported for each group (normolactatemia and hyperlactatemia) to address any distortion of study results.

We will avoid publication bias by attempting to publish the study irrespective of its conclusions.

## Discussion

Even though hyperlactatemia is common in tumor craniotomy patients, little is known of the underlying pathophysiology and the clinical effect of this phenomenon. The results of this study will provide new knowledge about the incidence and possible risk factors for hyperlactatemia in patients undergoing tumor craniotomy, as well as the potential association with functional outcome. It will also explore the role of the surgical stress response and glucocorticoid-associated insulin resistance for the development of hyperlactatemia and provide an indication of the pathophysiological significance for the brain by measuring the net cerebrovascular flux of lactate.

Previous studies on this subject [3–7] have been retrospective and may therefore have been susceptible to selection bias. With a prospective study we hope to avoid such bias by sampling data according to a prespecified protocol. There are, however, possible contributing factors to hyperlactatemia that we have not accounted for in our design. Thus, perioperative rhabdomyolysis may increase S-lactate [23]. In neurosurgery, rhabdomyolysis has been reported amongst patients who are placed in the lateral position, and for those who undergo surgery lasting more than 5 hours [16]. Myoglobin, creatine kinase, lactate dehydrogenase and creatinine are measured in our department only if there is clinical suspicion of rhabdomyolysis or kidney failure. We would most likely detect severe rhabdomyolysis, as we routinely monitor patient mobility, urine output and electrolyte levels. As part of our study design, we record perioperative positioning, duration of surgery, and BMI as possible contributing risk factors for hyperlactatemia.

Additionally, the type and volume of intravenous fluid administration may decrease or increase lactate levels by dilution or exogenous contribution, respectively. The intravenous fluid of choice in our department is isotonic saline; selected patients may receive hypertonic saline or Ringer lactate on specific indications. We do not use mannitol. Intravenous fluid type and volume in each perioperative phase will be reported in the final manuscript.

Another limitation of our study is the time period for lactate measurements. Due to the organization of perioperative care, we cannot measure S-lactate for longer that 6 hours postoperatively and therefore cannot differentiate between patients with late, prolonged, or short-lived hyperlactatemia.

An observational study design makes it possible to address multiple possible risk factors at once, which is a necessary approach when investigating a multifactorial phenomenon [24], such as hyperlactatemia. Many risk factors, however, may interact with each other. An example of this is the interaction between tumor volume and glucocorticoid dose. Tumor cells produce lactate, a process known as the Warburg effect [25]. A large tumor load may therefore contribute to elevated lactate levels [26]. Furthermore, voluminous and infiltrating brain tumors bring about peritumoral edema with increased intracranial pressure, a condition that is typically remedied with high-dose glucocorticoids, a drug class which may raise lactate through insulin resistance with hyperglycemia [27]. Tumor volume and glucocorticoids are thus interacting risk factors that contribute to lactate production through different mechanisms.

Moreover, lactate production by the tumor itself may be notably higher in patients with brain metastasis and extracranial primary tumors. We expect that these patients will exhibit higher initial lactate levels, but an unchanged "pure" perioperative contribution to the lactate load (see “Definitions and calculations”). Conversely, we expect that initial lactate levels are lower in patients who have received preoperative chemotherapy, radiation or immunotherapy, due to a reduction in tumor burden.

Brain tumors are very diverse, but it is unknown whether the lactate profile and time course differs by tumor type. We have chosen to include patients with meningiomas in our study, as they are classified as brain tumors by the American Association of Neurological Surgeons, and because previous studies have reported on the occurrence of hyperlactatemia even in patients with this tumor type. In the future, it also will be interesting to assess the effect of craniotomy on hyperlactatemia in patients with other surgical (e.g. neurovascular) indications.

While observational studies may be helpful at recognizing associations between variables, they are not designed to study causality. This study may thus help uncover associations between hyperlactatemia and potential risk factors, which subsequently will need further scrutiny to suggest potential causality. We therefore hypothesize that glucocorticoid-induced insulin resistance is a major risk factor of hyperlactatemia, i.e. that there is an association between glucocorticoid doses, markers of insulin resistance, and arterial lactate levels. If this hypothesis appears to be corroborated and if hyperlactatemia appears to be an independent risk factor of functional outcome, a randomized trial of two different doses of perioperative glucocorticoid may be planned.

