### Hyperlactatemia in brain tumor surgery: Pathophysiological implications

The cause of hyperlactatemia in brain tumor surgery is debated. Both tumor characteristics [10, 12–14], comorbidity [15], perioperative rhabdomyolysis [16], length of surgery [7], and type of anesthesia [17] have been suggested to play a part.

Lactate is well-known as a marker of global or regional ischemia, but as an additional consideration hyperlactatemia is also a marker of increased non-oxidative glycolysis and may be induced by hyperglycemia in healthy subjects [18]. Insulin resistance is a common side effect of glucocorticoid treatment and can also be induced in healthy subjects after short-term treatment [19]. As the majority of patients undergoing tumor craniotomy are treated with glucocorticoids either preoperatively (especially prednisolone to reduce edema and thus intracranial pressure), intraoperatively (especially dexamethasone, to reduce the perioperative stress response) or both, glucocorticoid-associated insulin resistance is an attractive explanation of hyperlactatemia after tumor craniotomy.

Lactate has previously been shown to act as a substrate for the brain in conditions with hyperlactatemia such as physical activity or lactate infusion [20]. It is therefore likely that perioperative hyperlactatemia associated with tumor craniotomy is also associated with increased cerebral lactate metabolism and, therefore, a net cerebrovascular lactate influx (i.e., a positive arterial to jugular venous concentration difference). This has never been addressed and would contrast with the usual finding of a slight net cerebrovascular lactate outflux from the brain to the bloodstream (i.e., a negative arterial to jugular venous concentration difference) at normal serum lactate.

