### Definitions and calculations

Hyperlactatemia is defined as the measurement of at least one value of S-lactate > 2.2 mmol / L during the observation period starting at surgical incision and ending after 6-hours of observation in the Post Anesthesia Recovery Unit.

Peak lactate is defined as the highest value of S-lactate measured during the observation period.

Mean S-lactate is calculated as the area under the curve for S-lactate over time during the observation period, divided by the duration in hours. This is calculated to estimate the “total” lactate load regardless of whether the triggers occur pre-, intra- or postoperatively.

Intra- / postoperative lactate excess is calculated as mean S-lactate minus S-lactate at surgical incision. This is calculated to estimate the "pure" perioperative contribution to the lactate load.

Arterio-venous concentration difference (a-jD) for lactate, glucose, and oxygen: the concentration in jugular bulb blood minus the concentration in arterial blood.

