#### Exploratory endpoints

Tumor type, location and estimated volume on preoperative MRI scan.BMI and comorbidity (Charlson Comorbidity Index), with focus on insulin dependent or non-dependent diabetes mellitus type 1 or 2 and liver / kidney disease.Neurological deficits at admission and at discharge. The deficits are assessed by the admitting and discharging clinician through standard neurological examination (mental status, cranial nerves, motor system, reflexes, sensation, and cerebellar function).Preoperative chemotherapy, radiation, or immunotherapy.Dose and duration of pre-, intra-, and post-operative treatment with glucocorticoids (expressed as cortisol equivalents in mg).Surgery duration (minutes) and surgery events (such as other procedures during the surgery and complications, using Landriel Ibañez classification).Position during surgeryComplete or incomplete total resection of tumor, as indicated by the neurosurgeon in the operative report.Type of anesthesia: total intravenous anesthesia, inhalation anesthesia, awake craniotomy.Intra- and post-operative hypotension (defined as MAP < 60 for > 15 min or MAP < 30% of preoperative resting MAP for > 15 min) and treatment with vasopressors (ephedrine, noradrenaline, methoxyarene) in mg for total surgery duration.Perioperative fluid therapy volume and type, as well as total urine output in mL / hour during surgery and in the Post Anesthesia Recovery Unit.Estimated blood loss and blood transfusion volume.Perioperative blood gas parameters: pH, glucose, PaO_2_, PaCO_2_, Base Excess, Hb, HCO_3_, Na, K, Cl.Postoperative nausea, vomiting and pain. Pain assessed by numeric or visual rating scale 0–10.Mobilization time to upright sitting position in the Post Anesthesia Recovery Unit, measured in hours.

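### The hyperlactatemia definition, the lactate excess and the sub-study IV endpoint do not separate infused from endogenous lactate, although the protocol recognises that fluids can add lactate

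*Protocol article*

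**What the plan says.** **Exposure.** Protocol article, Definitions and calculations: "Hyperlactatemia is defined as the measurement of at least one value of S-lactate > 2.2 mmol / L during the observation period". The period runs from incision to the end of six hours in the recovery unit. No exception is made for lactate given by infusion. The same section defines an intra-/postoperative lactate excess as mean S-lactate minus the value at incision, and presents it as the perioperative contribution alone.

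**Fluids.** The Discussion introduces "possible contributing factors to hyperlactatemia that we have not accounted for in our design", treats rhabdomyolysis first, and then adds that "the type and volume of intravenous fluid administration may decrease or increase lactate levels by dilution or exogenous contribution, respectively". Isotonic saline is the fluid of choice, but "selected patients may receive hypertonic saline or Ringer lactate on specific indications". The handling stated there is: "Intravenous fluid type and volume in each perioperative phase will be reported in the final manuscript".

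**Use of the fluid data.** Exploratory endpoints lists "Perioperative fluid therapy volume and type". A secondary endpoint of sub-study II is the association of the listed pre- and intraoperative factors with hyperlactatemia, and Statistical analysis plans multivariate logistic regression for binary variables.

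**Endpoints affected.** Under Primary endpoints, sub-study I compares the change in mRS between patients with and without hyperlactatemia. Sub-study II reports the prevalence of hyperlactatemia. Sub-study IV takes the change in arterio-jugular lactate difference from first to last measurement, corrected for the oxygen difference. The Introduction says the brain uses lactate as a substrate "in conditions with hyperlactatemia such as physical activity or lactate infusion".

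**The concern.** The exposure is a measured concentration, and one of its possible causes is a treatment given to selected patients on indication. Those patients may differ from the rest in prognosis. If the infusion lifts some of them above 2.2 mmol/L, the hyperlactatemia group gains patients whose outcome reflects the indication and not lactate metabolism. If they do not differ in prognosis, the group is diluted with patients who would otherwise be normolactatemic.

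The lactate excess has the same weakness. It removes what was present at incision, but lactate infused after incision stays in.

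In sub-study IV an infusion between the first and last sample can move the endpoint in the hypothesised direction, net cerebral influx, for a reason unrelated to craniotomy.

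The end of the Discussion makes a possible randomized trial of glucocorticoid doses depend in part on hyperlactatemia appearing to be an independent risk factor of functional outcome. That conclusion should not rest partly on infused lactate.

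**Working it through.** The plan states no figure on this point, so there is none to reproduce. The check is a comparison of the sections, followed by illustrations of size.

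**1. Does any rule separate the two sources?**
- Hyperlactatemia: any value above 2.2 mmol/L. No.
- Lactate excess: only the incision value is subtracted. No.
- Sub-study IV: corrected for the oxygen difference only. No.
- Sub-study II secondary endpoint: asks whether fluid type and volume predict hyperlactatemia. This can show that infused lactate contributes, but it reclassifies nobody and leaves the sub-study II prevalence and the sub-study I groups as they were.

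**2. Confounding by indication, with no true lactate effect.** All inputs are assumptions: a share f of patients receives Ringer lactate; 80% of recipients and 48% of the others exceed 2.2 mmol/L; risk of a binary poor outcome (standing in for a worse mRS change) is r = 25% or 30% in recipients and 10% in the others.

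Risk if hyperlactatemic = [0.80·f·r + 0.48·(1−f)·0.10] / [0.80·f + 0.48·(1−f)]

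Risk if normolactatemic = [0.20·f·r + 0.52·(1−f)·0.10] / [0.20·f + 0.52·(1−f)]

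For f = 5%, r = 25%: (0.0100 + 0.0456)/0.496 = 11.2% and (0.0025 + 0.0494)/0.504 = 10.3%, so OR = (0.1121/0.8879)/(0.1030/0.8970) = 1.10.

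| f | Recipients among hyperlactatemic | Risk difference, r = 25% to 30% (points) | Spurious OR |
|---|---|---|---|
| 5% | 8% | 0.9 to 1.2 | 1.10 to 1.13 |
| 10% | 16% | 1.7 to 2.3 | 1.19 to 1.25 |
| 15% | 23% | 2.5 to 3.3 | 1.26 to 1.34 |

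For scale, the planning rates of 15% and 7% in Sample size calculation differ by 8 points, an OR of (0.15/0.85)/(0.07/0.93) = 2.34.

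**3. The same mechanism with other assumptions.** Baseline risk 7%; half of the otherwise normolactatemic recipients pushed above 2.2; recipients' risk 15% to 25%; f = 5% to 20%; true prevalence 32% to 68% (the range cited in the Introduction). The spurious difference runs from 0.3 to 4.1 points. Example at prevalence 50%, f = 20%, recipients' risk 25%: (0.15×0.25 + 0.40×0.07)/0.55 = 11.9% against (0.05×0.25 + 0.40×0.07)/0.45 = 9.0%, a difference of 2.9 points.

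**4. Dilution only.** Here infusion-made cases carry the normolactatemic risk of 7%, and again half of the otherwise normolactatemic recipients cross the threshold. Observed prevalence = true prevalence + (1 − true prevalence)·f·0.5. Power is for 15% against 7% with 450 patients, two-sided 0.05.

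| True prevalence | f | Observed prevalence | Infusion-made share of hyperlactatemic | Power (without infusion) |
|---|---|---|---|---|
| 50% | 5% | 51.2% | 2.4% | 0.757 (0.776) |
| 50% | 20% | 55.0% | 9.1% | 0.696 (0.776) |
| 32% | 5% | 33.7% | 5.0% | 0.717 (0.744) |
| 32% | 20% | 38.8% | 17.5% | 0.633 (0.744) |

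Steps 2 and 3 push the estimate away from no association and step 4 pulls it towards none, so even the direction of the net bias is not fixed in advance.

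**5. Sub-study IV.** One or two recipients among 20 are 5% or 10% of the data. The documents give nothing from which to calculate how far they would move the mean.

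**6. Which restriction works?** Excluding only recipients infused before their first value above 2.2 could leave in those who never exceed it. In the step 2 setting with f = 10% and r = 30%, if every hyperlactatemic recipient is removed and the others stay, the risks are 10.0% against (0.02×0.30 + 0.468×0.10)/0.488 = 10.8%, an OR of 0.92. The bias changes sign. Excluding all recipients gives 10% in both groups and an OR of 1.

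**The case against.** **A full definition of models belongs to the SAP.** The article names no covariates for any model and says a statistical analysis plan will be made public. Adjustment for fluids in sub-study I may be there. This stands: a reader might infer that sub-study I will be left unadjusted, and the article does not say so. The point is therefore limited to definitions the article does fix, against a source of lactate it names itself.

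**Fluids are not ignored.** A reader might infer that the plan merely reports fluid volumes. The documents do not support that. Type is recorded as well as volume, both are candidate risk factors in sub-study II, and Bias and confounders says the major factors influencing lactate are investigated as exploratory endpoints. That covers the question of what predicts hyperlactatemia. It does not cover the exposure as carried into sub-study I.

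**Influx of infused lactate is real.** A reader might infer that sub-study IV would record a false influx. It would not: the Introduction itself names lactate infusion as a condition in which the brain uses lactate. Only attribution to craniotomy-related hyperlactatemia is in question, and nothing shows that any of the 20 patients will be a recipient.

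**The limitation is disclosed and probably small.** Saline is the fluid of choice and only selected patients may receive anything else, so low usage is at least as plausible as high. This also stands as to size. Disclosure does not remove the mixing, however, and the data needed to examine it are already collected.

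**Conclusion.** The point holds in this limited form. Followed as written, the hyperlactatemia definition, the lactate excess, the prevalence in sub-study II and the sub-study IV endpoint mix infused with endogenous lactate, while the Discussion recognises that source and places it among factors outside the design. Testing fluids as a risk factor in sub-study II does not undo the mixing.

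The size cannot be fixed from the documents: neither the share of recipients, nor the volumes, nor their prognosis is given. On the assumptions shown, the spurious OR is about 1.1 at 5% use and 1.26 to 1.34 at 15%; the alternative assumptions give 0.3 to 4.1 points against a planned difference of 8. The effect is small if use is rare and larger if use is common or goes to sicker patients. A claim that the bias is known to be large would go beyond the documents. The change is worth making because it is cheap and protects the independent-risk-factor conclusion.

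**What to change.** 1. **Sub-studies I and II.** Add a prespecified sensitivity analysis that excludes every patient given lactate-containing fluid during the observation period, whether or not their lactate exceeded 2.2 mmol/L.
2. **Continuous lactate models, including the lactate excess.** Include lactate-containing fluid volume as a covariate, and state that the excess as defined includes infused lactate.
3. **Sub-study IV.** Show the result with and without patients, or paired samples, exposed to a lactate-containing infusion. Do not attribute influx in those samples to craniotomy-related hyperlactatemia.
4. **Conclusion.** State that hyperlactatemia is an independent risk factor only if the restricted analysis agrees with the main one.

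**Cost.** Analysis wording. Fluid type and volume by phase are already collected; a sample-level split in sub-study IV also needs the infusion start time from the record. The restricted analysis loses some patients: about 23 of 450 at an assumed 5% use (0.05 × 450 = 22.5) and about 68 at 15% (0.15 × 450 = 67.5). Fluid practice is unchanged.
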